**Methods:**

DigiPuR is a randomized controlled trial comparing a digital aftercare service with regular aftercare (TAU) (planned *N* = 150, 25 children/adolescents, 25 parents, and 25 teachers in each group). In the intervention group, direct communication via secure and regular video calls until 8 weeks after discharge and a secure messenger system between the hospital, family, and school, as well as, if needed, external support systems, are established. A longitudinal pre-post-follow-up assessment at admission, discharge, and 8, 24, and 36 weeks after discharge takes place supplemented by a daily smartphone-based ambulatory assessment from a triadic perspective of patients, parents, and teachers. Primary outcomes include whether participants in the intervention group have fewer readmissions and higher treatment satisfaction and health-related quality of life as well as lower symptom severity than participants in the control group.

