### Randomization and blinding

Participants are assigned to the intervention or control group after having given written informed consent to participate in the study. Children or adolescents, their parents, and their teachers are always assigned to the same group. A randomization list with equal proportions of both groups was generated with the software R (based on the function “sample”) [48] before the start of the study. Participants are successively assigned to one of the two groups according to the order of their recruitment (date of written informed consent) using the randomization list. Only after inclusion in the study, DigiPuR study staff look up the assignment in the randomization list and record the assignment in the coding list, which is kept locked in a cabinet and only accessible to the study management. They inform therapists about the group assignment by e-mail and participants during the technical briefing by a video or phone call or on site at the hospital. Blinding of participants, case-leading therapists, and conducting study staff is not possible due to the different nature of treatment in the two groups. Data evaluation, however, is blinded, as group allocation is coded without knowledge of the data analysts.

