### Statistics

#### Calculation of the sample size

It is planned to include a total of *N* = 50 triplets (total sample approximately 150 persons) with 50 children and adolescents (*n* = 25 per group), one attachment figure (parent or caregiver) each and, if possible, at least one associated teacher each. Estimation of sample size is based on recently published randomized controlled trials, in which the efficacy of digital treatment for children and adolescents with mental disorders is compared with control conditions [75–77] and on the anticipated number of discharges of the department during the course of the study (average treatment duration of 3 months with approximately 10 children per ward).

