#### Statistical analyses

All analyses are conducted using R software [48]. All outcome variables measured pre-post-follow-up will be analyzed with separate mixed ANOVAs. Preprocessing of the data and calculation of individual values will be done according to the respective manual. Predictors will be group (intervention vs. control) and time point, as well as their interaction. Treatment success would be demonstrated by a significant interaction effect of group and time point, being shown, through adequate post hoc test, to be due to different time-effects in the two groups. We do not necessarily expect the intervention group to improve in absolute values over time, as measures can decline after discharge. Rather, we expect the intervention group to develop better over time than the control group, meaning that even a stabilization of values might be considered a success. This better development in the intervention group than in the control group should be evident in the information provided by patients themselves, as well as by parents and teachers.

The successful reintegration into daily (school) life is conceptualized besides the pre-post-follow-up assessment by the data collected in the ambulatory assessment. All ambulatory assessment data will be analyzed with multi-level models [78]. We expect the reports from patients, parents, and teachers in the intervention group to show a significantly more positive trend over time in terms of their general well-being, affect, sleep quality, school absenteeism, situation in class, and the relationship with parents, peers, and teachers, than those in the control group. Statistically, these effects are shown by a significant interaction of the within-person time trends of these reports with group membership, being due to participants in the intervention group developing better (or less bad) than participants in the control group. Variables will be adequately centered, and appropriate fixed and random effects will be included in the models.

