Few missing data are expected due to ongoing monitoring. Missing data from single items of the standardized questionnaires will be handled appropriately according to the instructions in the manual. In case of complete questionnaires missing for a participant, this participant will be excluded from all ANOVAs containing this questionnaire. As multi-level models can handle missing data quite well, if they are at least missing at random, no data will be excluded from those analyses. However, appropriate variables (e.g., age, symptom severity) will be used to investigate if the missingness structure can be explained by them, rendering it to be not at random. In that case, those variables will be included in the according models to account for this non-randomness.

Due to the confidentiality of patient health data, data sets cannot be made publicly available. Access is only granted to study management who supervise data management and have a duty of confidentiality.

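### One missed questionnaire removes a participant from the whole repeated-measures ANOVA of that outcome, which costs precision on two primary outcomes and selects the analysed set after randomisation

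*Protocol article*

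**What the plan says.** Under Statistical analyses, the protocol article assigns one method to every questionnaire outcome: "All outcome variables measured pre-post-follow-up will be analyzed with separate mixed ANOVAs". The predictors are group, time point and their interaction, and the criterion is fixed: "Treatment success would be demonstrated by a significant interaction effect of group and time point". The Hypotheses section and Table 1 place two of the four primary outcomes in this scheme: health-related quality of life (KIDSCREEN-27) and symptom severity (DISYPS-III SCREEN). The Abstract gives the schedule: "A longitudinal pre-post-follow-up assessment at admission, discharge, and 8, 24, and 36 weeks after discharge takes place".

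The same section sets the missing-data rule for these ANOVAs: "In case of complete questionnaires missing for a participant, this participant will be excluded from all ANOVAs containing this questionnaire". The next sentence treats the daily ambulatory data differently: "As multi-level models can handle missing data quite well, if they are at least missing at random, no data will be excluded from those analyses". It adds that variables explaining missingness will be included in those models.

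The section expects few missing data because of ongoing monitoring but gives no rate. The Evaluation section says staff will inquire by phone when multiple data are missing.

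**The concern.** The exclusion sentence does not say whether a questionnaire must be missing at one time point or at all of them. The method settles it: a mixed ANOVA with time as the within-person factor uses only people with a value at every wave it includes. A family that answers at weeks 8 and 24 but misses the week-36 link therefore contributes nothing to the test of that outcome.

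Two things are at stake. First, the trial plans only 25 patients per arm, and the rule discards values already collected. Second, whether someone completes all surveys is known only after randomisation, so the groups compared are no longer those that were randomised. The article recognises that multi-level models avoid the exclusion, yet it reserves them for the ambulatory data, which are secondary. Two primary outcomes thus get the less robust treatment.

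**Working it through.** **Inputs from the article**
- Patients: "with 50 children and adolescents", 25 per group (Calculation of the sample size). Allocation: "A randomization list with equal proportions of both groups was generated" (Randomization and blinding).
- Waves: five. Admission and discharge are standard hospital assessments run by trained staff. Weeks 8, 24 and 36 are online surveys answered from home within one week (Pre-post-follow-up assessment).

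**The plan's own figure.** The 25 per group cannot be reproduced. The article says "Estimation of sample size is based on recently published randomized controlled trials" and refers to expected discharges, but gives no effect size, SD, alpha, power or dropout allowance.

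**Assumptions (none from the article).** Two-sided 5% level, 80% power, and 5% or 10% missed independently at each of the three remote surveys.

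**Step 1: complete cases.** The share retained is (1 − p)³.
- p = 0.05: 0.95³ = 0.857, and 0.857 × 25 = 21.4, about 21 per arm.
- p = 0.10: 0.90³ = 0.729, and 0.729 × 25 = 18.2, about 18 per arm.

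The share of answered post-discharge questionnaires that is discarded is 1 − (1 − p)²: 1 − 0.9025 = 10% at p = 0.05, and 1 − 0.81 = 19% at p = 0.10.

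**Step 2: detectable difference.** The normal approximation is (1.96 + 0.842) × √(2/n). The t-test values are slightly larger.

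| n per arm | Normal approximation | t-test |
|---|---|---|
| 25 | 0.79 SD | 0.81 SD |
| 21 | 0.86 SD | 0.89 SD |
| 18 | 0.93 SD | 0.96 SD |

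Part of this rise is unavoidable. At p = 0.10 only 0.90 × 25 = 22.5 per arm are observed at any one wave, for which the detectable difference is about 0.85 SD. The step from about 0.85 to 0.96 SD is due to the deletion rule. If the same people missed all three surveys, 22.5 per arm would be complete and the figure would stay at about 0.85 SD.

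The planned test is a repeated-measures interaction whose power depends on correlations the article does not give. These figures therefore show relative loss only.

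**Step 3: bias.** Large-sample simulation with a true effect of 0.50 SD on change from discharge and equal between-wave correlations of 0.5 to 0.7. Dropout after week 8 depended on the week-8 score, with about 28% of controls and 19% of intervention patients lost.
- Completers' cross-sectional difference at week 8: about 0.42 SD.
- Completers' difference at discharge: about −0.04 to −0.06 SD, an imbalance created by the selection.
- Difference in change from discharge, which is what the interaction tests: 0.46 to 0.48 SD at week 8 and 0.50 SD at weeks 24 and 36. Across runs with slightly different settings the week-8 value was about 0.46 to 0.49 SD.

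In a variant where people could drop out after either week 8 or week 24, depending on the last score, complete cases gave 0.46 to 0.48 SD at weeks 8 and 24 and 0.50 SD at week 36. Maximum likelihood on all observed values gave 0.49 to 0.51 SD at every wave.

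**The case against.** The strongest reply is that the rule will rarely apply. The article expects few missing data, checks returns continuously and phones families. Admission and discharge questionnaires are collected in hospital. Assessments run the same way in both arms, and both arms answer the daily app until week 8. Deletion is per questionnaire, so an excluded person still counts for other instruments and in the multi-level models. Satisfaction is measured once, and readmissions draw on hospital documentation, so two of the four primary outcomes escape the problem.

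Much of this stands, and it limits the size of the point. Three stronger readings go too far:
- A reader might put all four or five waves at equal risk. At 10% per wave that leaves about 16 or 15 of 25 per arm (0.9⁴ = 0.656, 0.9⁵ = 0.590) and a detectable difference of 1.02 to 1.06 SD. The staff-run hospital assessments make this unlikely.
- A reader might take the completers' week-8 difference of about 0.42 SD as the bias. That is a cross-sectional contrast. The stated criterion is differential change, where the shortfall is much smaller.
- A reader might say flatly that the comparison is biased. Selection after randomisation opens that possibility, but under data missing completely at random there is no bias, and the article gives no dropout data by arm.

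The reply does not remove the point. An expectation without a rate is no safeguard. The phone inquiry is triggered by multiple missing data, whereas one missed wave is enough for exclusion. The rule is also written into the article, so it is not a detail left for an analysis plan.

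**Conclusion.** The point holds as a stated analysis choice that wastes observed data on two primary outcomes. Its most certain consequence is lost precision. With 5 to 10% missed independently at each remote survey, about 21 to 18 of 25 per arm are analysed, and the guide figure for the detectable difference rises from 0.81 to about 0.89 to 0.96 SD. Clustering of missed surveys in the same people makes the loss smaller, and higher missingness makes it larger.

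Bias is secondary and depends on the mechanism. It is nil under data missing completely at random. In simulated score-dependent dropout it was a shortfall of about 0.01 to 0.04 SD from a true 0.50 SD at week 8, and about none at week 36. It could be larger here because, under Participants and recruitment, an emergency inpatient stay of more than 2 weeks ends participation. Loss of later questionnaires may then be tied to deterioration and to readmission, itself a primary outcome. The article does not allow this to be quantified. All missingness rates, correlations and effect sizes used are assumptions.

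**What to change.** Replace the mixed ANOVAs of the pre-post-follow-up outcomes by a linear mixed model for repeated measures:
- Fixed effects for group, categorical time and their interaction, with discharge modelled as an outcome.
- REML estimation with Kenward-Roger degrees of freedom.
- A covariance structure named in advance, with a simpler stated fallback if the model does not converge. An unstructured matrix over five waves has 5 × 6 / 2 = 15 parameters, which is demanding with 50 patients.
- Every randomised participant with any observed value, analysed as randomised. Requiring at least one post-discharge value would itself be an exclusion after randomisation, and is unnecessary once discharge is an outcome.

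Keep the complete-case ANOVA as a sensitivity analysis. The planned check for variables that explain missingness can be extended to these models.

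The cost is small. R and multi-level models are already planned, and with complete data the result should be close to the ANOVA's. Because recruitment was already under way at the article's version date, the change needs a documented amendment before the data are analysed.

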#### Data security and storage

Procedure for data management was approved by the data protection officer and the IT security officer of the University Hospital Tuebingen, Germany. The collection and storage of all data is pseudonymized and stored for 10 years. All questionnaires are labeled with an anonymous personal code of the participant. Data can only be assigned to individuals based on a coding list, which is continually updated by hand, kept locked, and only accessible to study management. The coding list will be destroyed at the end of the study.

##### Pre-assessment

All information used in paper form for the study at admission and discharge will be kept in the participating child’s or adolescent’s medical record and is additionally entered pseudonymously into a spreadsheet file, so that the information can only be assigned to the other data by the personal code.

##### Post- and follow-up assessment

Data collected with SoSci Survey [50] at post and follow-up is protected by SSL encryption (HTTPS) Extended Validation (EV) both when filling in the questionnaire and when retrieving the collected data. Data is hosted on an ISO27001-certified server in Germany. The provider protects against data loss and access by third parties by means of a firewall.

##### Ambulatory assessment

Data from the ambulatory assessment will be encrypted, ensuring that the collected data cannot be accessed by unauthorized persons even if the device is lost. All data connections (i.e., both the communication between the smartphone and the server and the communication between the server and the researcher’s browser) are encrypted using 256-bit SSL encryption. Furthermore, participants are instructed not to indicate personal data that could be used to identify the children and adolescents, parents, teachers, or other persons (e.g., names, locations, etc.), neither when answering the questions nor in the messages in the app *movisensXS* [49].

##### Video calls

The program VidyoConnect [51] for the video calls in the intervention group is a standard software certified by the university hospital. No data is recorded during use. Participants are instructed not to produce and distribute any audio or visual material of the sessions.

##### Cloud

The firewall-protected cloud of the university hospital is used for the exchange of files with participants. It meets particularly high security requirements and is approved for the storage of anonymized or pseudonymized patient data. Participants receive a link with a password to their own folder in which the therapist can store worksheets (e.g., documentation of weekly goals) and information in PDF format. There is never a name or other identifiable information on the materials. Access to the folder in the cloud is restricted to the therapist and the respective participant.

##### Storage locations and dissemination

At the end of the study, all participant data is deleted from the servers used by *movisensXS* [49] and SoSci Survey [50] as well as the cloud of the university hospital. From this point on, the pseudonymized data of the participants are stored in the form of a spreadsheet file exclusively on the drive of the university hospital, to which only authorized staff have access, and evaluated with the help of statistical analysis software. Paper-pencil data are entered twice, compared with the help of an R-script [48] and checked for errors. Evaluation data from the online surveys are summarized into a data set by means of an R-script [48] without reference to specific individuals. Participants do not receive individual feedback on their data. Instead, the anonymized results will be published in scientific journals and presented at conferences and in the hospital. The study is monocentric and has no data monitoring committee as it is a low-risk intervention.

## Discussion

DigiPuR is a longitudinal randomized controlled trial comparing regular aftercare (TAU) in the control group with a novel, digital aftercare service in the intervention group. In the intervention group, regular video calls take place with all parties involved during the reintegration phase until 8 weeks after discharge. In addition, patients, parents, and teachers have a direct communication channel to the therapist via a secure messenger system. This is intended to stabilize treatment successes after discharge and, if necessary, to accompany the transition to outpatient services. This paper describes the naturalistic parallel group study design of DigiPuR and its evaluation. Besides pre-post-follow-up surveys, an ambulatory assessment provides ecologically valid daily data on the reintegration phase from the triadic perspective of patients, parents, and teachers. Psychological strains and exacerbations should thus be recognized at an early stage, addressed and hence readmissions reduced.

Limiting factors that should be considered in the interpretation of the results include that questionnaires in the evaluation are used across the age range of both children and adolescents. This was necessary to ensure sufficient comparability but implied adapting item formulations to a wide age range with possible limitations regarding psychometric properties of questionnaires used. Second, due to the different nature of treatment in the two groups, blinding of participants, therapists, and study staff is not possible. Data analysis, however, is blinded, as group allocation is coded without knowledge of the data analysts. Third, the time required for aftercare appointments and the assessments may be a barrier to study participation and is likely to be weighed against the personal benefits of increased support during the reintegration phase. However, the decision for study enrollment takes place before randomized group assignment, so any potential bias should not affect group comparisons.

Results will show whether DigiPuR can increase participants’ health-related quality of life and reduce a worsening of symptoms as well as rehospitalizations. It is expected that the digitally supported, seamless, and regular aftercare appointments involving family and school attachment figures in the intervention group will contribute to a successful reintegration. DigiPuR is designed to improve cross-sectoral child and adolescent psychiatric health care, but in doing so, also to provide further training in this area for teachers in the educational system. Expanding the spectrum of traditional services by establishing digital media as contemporary, widespread, and practicable tools in daily clinical practice can improve child and adolescent psychiatric care because a wider spectrum offers more treatment options in general, as well as more possibilities to adapt treatment to the characteristics and needs of individual patients [34, 79]. The COVID-19 pandemic, as an unforeseen crisis that came along with considerable mental stress for many children and adolescents [80–83], may simultaneously act as an accelerator in establishing E-Mental-Health in health care [84]. In this regard, the expansion of digital infrastructure that occurred in the wake of the COVID-19 pandemic and the associated broader use of digital media can be expected to have a beneficial impact on DigiPuR. Barriers for using digital media can be expected to decrease further, willingness to communicate without being tied to a specific location will increase, and technical skills will improve. E-Mental-Health is expected to advance mental health care by being accessible, available, attractive, and cost-effective [85] and should go along with collaborative research from science and practice in naturalistic settings [86]. In case of efficacy and successful implementation of DigiPuR in clinical daily processes, an integration of DigiPuR into regular care is possible and planned.

### Trial status

The trial is ongoing (10-29-2021, version 1, start of recruitment: March 2021, estimated end of recruitment: June 2022)

## Data Availability

Data cannot be made available due to confidentiality of patient health data. However, the statistical code and all study materials will be available from the corresponding author on reasonable request, and any questions about the procedure are welcome. Contact for more information on the study: [contact] or [name].

## Abbreviations

BSCL: Brief Symptom Checklist
DigiPuR: Study name (Digital gestützte Psychotherapie und Reintegration – Digitally supported psychotherapy and reintegration)
DISYPS-III SCREEN: Diagnostic System for Mental Disorders according to ICD-10 and DSM-5 for Children and Adolescents - III Screening questionnaire
EBI: Eltern-Belastungs-Inventar (German version of the Parenting Stress Index)
FBB: Fragebogen zur Beurteilung der Behandlung (German Questionnaire for the assessment of treatment)
KIDSCREEN-27: KIDSCREEN questionnaire with 27 items
PANDA: App name in the ambulatory assessment
SSKJ 3-8R: Fragebogen zur Erhebung von Stress und Stressbewältigung im Kindes- und Jugendalter – Revision (German Questionnaire for the Survey of Stress and Stress Coping in Childhood and Adolescence)
SUS: System Usability Scale
TAU: Treatment-as-usual
